### Sample size calculation

2.6

The sample size was determined based on the primary outcome: change in PSQI score from baseline to Week 8. A superiority trial design employing a two-sample mean comparison was used to assess whether EA demonstrates clinically meaningful superiority over SEA. Based on prior reports of the minimal clinically important difference (MCID) for PSQI in traditional Chinese medicine trials (1.69–1.80) (43, 44), the superiority margin(*δ*) was set at 1.8. The sample size per group (n) was calculated using the formula (45):

$$n=[{\left(z_{1-\alpha }+z_{1-\beta }\right)}^{2}\sigma^{2}(1+1/K)]/{\left(\in -\delta \right)}^{2}.$$

where: n is the sample size of per group, σ is the estimated standard deviation, ϵ is the difference between treatment and control group, δ is the superiority margin.

Based on a prior single-centre RCT, PSQI scores decreased by 5.67 in the EA group and 1.83 in the SEA group, yielding ϵ = 3.8 (33). Therefore, we set ϵ = 3.8, assumed a standard deviation σ = 4, a one-sided significance level α = 0.025 (z_1 − α_ = 1.960), a type II error *β* = 0.1 (z_1 − β_ = 1.282), and an allocation ratio K = 1 (1:1 allocation between the experimental and control groups).

The calculated sample size per group is n = 85. Accounting for a 20% attrition rate, the final sample size is adjusted to 107 participants per group, resulting in a total enrolment target of 214 older adults with insomnia disorder.

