### Randomisation and blinding

2.7

Participant randomisation will be conducted via a centralised, web-based system. An independent statistician, uninvolved in trial execution, will generate the allocation sequence using SAS 9.4 software, employing stratified block randomisation with two stratification factors: study site and current use of hypnotic medication. Variable block sizes (2, 4, 6, or) will be used. Following confirmation of eligibility, designated randomization personnel at each study site will input the participant’s information into the central system to obtain a unique identification number and treatment allocation. Access to this system will be restricted to randomisation personnel and data monitors; all other study staff, including outcome assessors and statisticians, will remain blinded. Randomisation personnel will only be able to view participants and allocations within their respective centre.

This trial adopts a single-blind design, with participants blinded to group allocation. Due to the nature of EA, blinding of acupuncturists is not feasible. Participants will be informed during enrolment that they have an equal probability of being assigned to either intervention group. To ensure effective blinding, sham acupuncture needles with validated manufacturing standards and prior use in clinical trials will be used for the SEA group (35–37). Participants will undergo treatment in a supine position while wearing eye masks, and all interventions will be conducted in separate rooms to minimise cross-group contamination. Blinding integrity will be assessed at week 8, after the final treatment session, by asking participants to guess their group assignment. Apart from the acupuncturists administering the intervention, all other study personnel, including outcome assessors and statisticians, will remain blinded until the trial’s conclusion, at which point routine unblinding will be performed. All research staff will undergo comprehensive training prior to trial initiation and will strictly adhere to role separation protocols across departments.

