#### Primary outcome

2.9.1

**PSQI** is a validated, widely used tool for assessing sleep disorders (49). It is easy to administer and demonstrates high reliability and validity (50). The PSQI evaluates sleep quality over the previous month in individuals with organic or non-organic sleep disorders. It comprises 23 items, grouped into seven components: subjective sleep quality, sleep latency, sleep duration, habitual sleep efficiency, sleep disturbances, use of sleep medication, and daytime dysfunction. Each component is scored from 0 to 3, yielding a total PSQI score ranging from 0 to 21. A score > 7 indicates poor sleep quality, with higher scores denoting greater impairment (50).

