### Statistical analysis

2.12

Statistical analyses will be conducted using SAS version 9.4 (SAS Institute, Cary, NC). Descriptive statistics will be reported as mean ± standard deviation (Mean ± SD) for normally distributed continuous variables with homogeneous variance, and as median with interquartile range [Median (P25, P75)] for non-normally distributed or heteroscedastic data. Categorical variables will be presented as frequencies and percentages. All analyses will follow the intention-to-treat (ITT) principle. Missing data due to participant dropout will be handled using the last observation carried forward (LOCF) method.

Baseline characteristics, including demographic variables and hypnotic medication use before and after the intervention, will be analysed as follows: Continuous data with normal distribution and homogeneity of variance will be assessed using the independent two-sample t-test; otherwise, the Mann–Whitney U test will be applied. Categorical variables will be analysed using the chi-squared test. For the primary and secondary outcome measures, repeated measures will be analysed using a linear mixed-effects model. Fixed effects will include intervention group, time, and their interaction (intervention × time), while a random intercept for each participant will be included as a random effect. Results will be reported as point estimates with 95% confidence intervals. All statistical tests will be two-sided, with a *p*-value < 0.05 considered statistically significant.

To assess potential heterogeneity in treatment effects and enhance the generalisability of the findings, exploratory subgroup analyses will be conducted based on key baseline characteristics. In particular, we will examine whether the primary and selected secondary outcomes differ among participants with common age-related comorbidities such as hypertension and diabetes. These analyses will be exploratory in nature and are intended to inform hypothesis generation for future studies.

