## Discussion

3

Age-related alterations in sleep–wake cycles and circadian rest-activity rhythms often present as fragmented nocturnal sleep and excessive daytime sleepiness in older individuals (65). While multiple clinical guidelines recommend non-pharmacological therapies—particularly CBT-I—as the first-line treatment (16, 17), accessibility to CBT-I remains limited in regions such as China (66), and its efficacy in elderly populations requires further substantiation. Consequently, hypnotic medications remain the primary treatment for insomnia disorder in older adults. However, diminishing therapeutic effects and concerns over adverse outcomes associated with long-term use warrant alternative therapeutic strategies. Acupuncture, a widely utilised non-pharmacological intervention, lists insomnia among its principal indications and is a promising avenue of research (67, 68). Nevertheless, definitive evidence on its efficacy and safety in older adults is lacking, necessitating rigorously designed, adequately powered multicentre randomised controlled trials—such as the present study. Insomnia disorder is now widely recognised as a distinct clinical entity that warrants independent diagnosis and treatment, irrespective of comorbid conditions (42). An expanding body of empirical evidence supports the effectiveness of insomnia-specific interventions even in the presence of comorbidities (69). Given the complex health profiles of older adults, many of whom present with chronic illnesses, we have implemented exclusion criteria to eliminate confounding conditions such as other sleep disorders, neuropsychiatric illnesses, cancer, or other life-threatening diseases. However, we have not excluded individuals with stable chronic diseases. This decision is based on two considerations: the high prevalence of chronic conditions in this population, which should be balanced across groups through randomisation; and the need to ensure ecological validity by maintaining a sample representative of the broader population of older adults with insomnia. As this is not a pharmacological trial, participants may either be using hypnotic medications regularly or not at all, provided their insomnia symptoms are chronic and stable, and they agree not to increase their medication use after enrolment. To ensure baseline equivalence, pre-enrolment hypnotic use will serve as a stratification factor. This inclusion criterion is consistent with acupuncture research conventions (30, 70, 71) and permits a meaningful evaluation of acupuncture’s therapeutic effect. Based on expert clinical consensus and our prior research, we have selected the acupoints and EA parameters for this trial. Fixed acupoints, derived from traditional Chinese medicine theory and clinical practice, include GV20, GV24^+^, EX-HN22, HT7, PC6, CV12, CV4, ST36, and SP6. In addition, following standard clinical acupuncture practice (72), acupuncturists will select adjunctive acupoints tailored to individual symptoms commonly observed in older adults with insomnia, potentially enhancing treatment efficacy. Given the typically prolonged duration and increased severity of insomnia in older adults, the intervention phase will last 8 weeks, with sessions conducted thrice weekly. A 12-week post-intervention follow-up will assess sustained effects. Assessments will occur at baseline, weeks 4 and 8 of intervention, and weeks 4 and 12 post-intervention (i.e., study weeks 12 and 20), allowing for the evaluation of both short-term and long-term outcomes. This follow-up structure aligns with previous randomised controlled trials investigating acupuncture for other forms of insomnia (30, 32, 70).

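### The primary model omits both randomisation strata and a baseline PSQI covariate, which gives away precision that could be had almost free

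*Protocol article*

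**What the plan says.** Randomisation and blinding (2.7) describes allocation as "employing stratified block randomisation with two stratification factors: study site and current use of hypnotic medication". There are five hospitals, so the two factors define ten strata. The Discussion gives the reason for the second factor: "To ensure baseline equivalence, pre-enrolment hypnotic use will serve as a stratification factor".

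The sample size section (2.6) defines the primary outcome as "change in PSQI score from baseline to Week 8". Table 1 schedules PSQI at weeks 0, 4, 8, 12 and 20.

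Statistical analysis (2.12) sets out the model for primary and secondary outcomes: "Fixed effects will include intervention group, time, and their interaction (intervention × time", and "a random intercept for each participant will be included as a random effect". Site, hypnotic use and baseline PSQI are not named as covariates there or anywhere else in the article. The section does not say whether week 0 is a level of time or is left out of the response. It also states "Missing data due to participant dropout will be handled using the last observation carried forward (LOCF) method".

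**The concern.** There are two separate issues.

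**Baseline.** The model does not regress the week-8 score on the baseline score. If week 0 is a level of time, the week-8 interaction is a difference in mean change, which subtracts baseline with a weight of exactly one. If week 0 is not a response, the contrast is a plain week-8 difference, which ignores baseline. Baseline adjustment estimates the weight from the data and so does at least as well as either in large samples.

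**Strata.** Stratified allocation balances the arms within site and hypnotic stratum. The treatment estimate then varies less between hypothetical repeats of the trial than under simple randomisation. A model that omits the strata may leave their contribution in its error term and report intervals that are too wide. Hypnotic use is a plausible predictor, because the PSQI components include "sleep disturbances, use of sleep medication, and daytime dysfunction".

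At stake is the precision of the primary comparison and, to a lesser degree, the calibration of its standard error.

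**Working it through.** **1. The plan's own figure.** Inputs from 2.6: expected difference 3.8, margin 1.8, SD 4, one-sided α 0.025, power 90%, 1:1 allocation.

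n = (1.960 + 1.282)² × 4² × 2 / (3.8 − 1.8)² = 84.06 (unrounded z), so 85 per group. Then 85/0.8 = 106.25, so 107 per group and 214 in total. The stated figures reproduce, and the formula assumes no covariate. With 85 per group the SE is 4 × √(2/85) = 0.614, and power is Φ(2.0/0.614 − 1.960) = 90.3%.

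**2. What baseline adjustment gains.** Let s0 and s8 be the SDs at weeks 0 and 8, and ρ their correlation.

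- Change contrast: variance proportional to s0² + s8² − 2ρ·s0·s8.
- Baseline-adjusted contrast: proportional to s8²(1 − ρ²).
- Difference: (s0 − ρ·s8)², which is never negative.
- Against an unadjusted week-8 score, the gain is ρ²·s8², also never negative.

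With s0 = s8, the adjusted variance is (1 + ρ)/2 of the change variance, a cut of (1 − ρ)/2. The article gives no ρ, so 0.3-0.7 is an assumption. Taking SD 4 as the SD of change:

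| ρ (assumed) | Variance cut | SE (from 0.614) | Power at 85 per group | n per group for 90% |
|---|---|---|---|---|
| 0.3 | 35% | 0.495 | 98.1% | 55 |
| 0.5 | 25% | 0.531 | 96.4% | 64 |
| 0.7 | 15% | 0.566 | 94.2% | 72 |

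If SD 4 is instead the SD of the week-8 score and that score is compared unadjusted, adjustment gives n = 77, 64 and 43 for the same ρ.

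**3. Unequal SDs.** Keep the SD of change at 4, so its variance is 16, and solve for s8:

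- s0 = 3, ρ = 0.6: s8 = 5, adjusted variance 25 × 0.64 = 16, gain 0%.
- s0 = 4, ρ = 0.5: s8 = 4, adjusted variance 16 × 0.75 = 12, gain 25%.
- s0 = 4, ρ = 0.2: s8 = 1.6, adjusted variance 2.56 × 0.96 = 2.46, gain 85%.

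The sign is certain. The size depends on inputs that the article does not give.

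**4. Strata and the standard error.** For a simple two-sample test, if strata explain a share R² of the variance of the analysed quantity, the unadjusted SE is too large by a factor 1/√(1 − R²). R² of 5% gives 1.026 (true two-sided α 0.044), and 20% gives 1.118 (α 0.028). This is not the planned model, so the planned form was also simulated: 214 patients, five sites by hypnotic use, permuted blocks, no treatment effect, 4,000 trials per scenario. The stratum effects were assumed.

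| Contrast at week 8 | Strata affect level only: model SE / true SE, α | Strata also affect change: model SE / true SE, α |
|---|---|---|
| Planned random-intercept model, change | 0.483 / 0.488, 0.056 | 0.491 / 0.486, 0.048 |
| Simple change-score test | 0.483 / 0.488, 0.052 | 0.501 / 0.486, 0.044 |
| Unadjusted week-8 score | 0.469 / 0.446, 0.037 | 0.533 / 0.441, 0.017 |
| Baseline and strata adjusted | 0.404 / 0.412, 0.053 | 0.404 / 0.402, 0.047 |

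Simulation error on α is about 2 × √(0.05 × 0.95/4000) = 0.007, so 0.056 is compatible with 0.05.

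**5. Which stratum terms matter.** On one simulated complete data set with week 0 as a level of time, adding site and hypnotic use as time-constant terms left the week-8 change contrast at −2.456 with SE 0.5046. Adding stratum × time terms moved it to −2.475, SE 0.499. Because last observation carried forward fills in dropouts, the planned data would also be close to balanced over visits.

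**The case against.** The strongest reply has three parts.

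First, this is a condensed article, its wording on fixed effects is not strictly exhaustive, and an unseen analysis plan may add terms. That is fair as far as it goes. But the article does not leave the model open: it lists the fixed and random effects, and that list is what is under review.

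Second, a reader might infer that the standard errors are simply wrong for a stratified design, with a true type I error of 2.8-4.4%. The documents do not support this. The endpoint is change to week 8. If week 0 is a level of time, strata that shift only the PSQI level cancel out of that contrast. Nothing in the article shows that strata predict change, and the sleep-medication component bears mainly on level, because regular users enter on a stable dose. Those percentages describe a simple change-score test under an assumed R². In the simulated case where strata did affect change, the planned model gave about 0.048. The larger discrepancies (0.037 and 0.017) arise only if an unadjusted week-8 score is tested.

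Third, a reader might infer that the trial is underpowered. It is not, on this ground: 85, 107 and 214 reproduce with no adjustment assumed.

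This reply removes any claim of invalid inference. It leaves the loss of precision from not adjusting for baseline.

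**Conclusion.** The omission is real, and correcting it is a nearly free improvement. It is not an error that threatens the result.

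- **Precision:** relative to the change contrast, baseline adjustment would cut the variance by 15-35%, assuming equal SDs and a correlation of 0.7-0.3. With unequal SDs the gain can be near zero or larger, so no single figure should be promised.
- **Standard errors:** they may be too large if the strata predict the analysed quantity. The effect is absent if strata affect only level and week 0 is a level of time, small for the change contrast in the planned model, and larger if an unadjusted week-8 score is tested. Where it occurs, it is conservative.
- **Validity:** the omission does not bias the estimate, inflate type I error or put the trial below its stated 90% power.

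The correlation, the SD at each visit and the strength of the strata are assumptions; the article gives none of them.

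**What to change.** State the role of week 0, then specify one of two forms.

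- **Preferred:** model PSQI at weeks 4, 8, 12 and 20 with group, categorical visit, group × visit, baseline PSQI, baseline PSQI × visit, site and hypnotic-use stratum, and take the group contrast at week 8 as primary.
- **If week 0 stays a response:** add stratum × visit terms, because time-constant stratum terms leave the change contrast unchanged. This deals with the strata but does not recover the baseline gain.

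Apply the same approach to each secondary outcome at the post-baseline visits where Table 1 schedules it: ISI and HADS at all four, MMSE at weeks 8 and 20, actigraphy and diary only up to week 8.

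The cost is wording, fixed before unblinding. Baseline PSQI, hypnotic use and site are already recorded. The preferred form adds nine parameters (one for baseline, three for baseline × visit, four for site, one for hypnotic use), a small price with 214 participants. The alternative adds 25 (five stratum terms and 5 × 4 = 20 interactions), a further reason to prefer the first.

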**Methods and analysis:**

This multi-centre, single-blind, randomised controlled trial will enrol 214 older adults with diagnosed insomnia disorder from five hospitals. Participants will be randomly assigned in a 1:1 ratio to receive either electroacupuncture or sham electroacupuncture. The electroacupuncture group will undergo treatment three times per week for 8 weeks. The sham electroacupuncture group will receive a non-penetrative placebo needle intervention at sham acupoints, with no electrical stimulation delivered despite connection to the electroacupuncture apparatus. The primary outcome will be the change in Pittsburgh Sleep Quality Index score. Secondary outcomes will include the Insomnia Severity Index, actigraphy-derived sleep parameters, sleep diaries, the Hospital Anxiety and Depression Scale, and the Mini-Mental State Examination. All outcomes will be assessed at baseline (week 0), during intervention (weeks 4 and 8), and during follow-up (weeks 12 and 20).

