#### Inclusion criteria

2.5.1

Participants must meet all of the following criteria:

Aged between 60 and 85 years (inclusive), regardless of gender.Meet the diagnostic criteria for insomnia disorder according to *Diagnostic and Statistical Manual of Mental Disorders, Fifth Edition (DSM-V)* (42).Have a PSQI score > 7.Have not taken hypnotic medications within the past 2 weeks, or are on a stable dose for at least 4 weeks.Provide written informed consent and agree to comply with all intervention procedures and assessments.

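### The random-intercept model pools one residual variance over five PSQI visits, so the SE of the week-8 contrast can be misstated in either direction

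*Protocol article*

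**What the plan says.** - **Model.** Section 2.12 of the protocol article specifies a linear mixed-effects model for the primary and secondary outcomes. The fixed effects are group, time and their interaction, and "a random intercept for each participant will be included as a random effect". It mentions no residual covariance structure, random slope or robust SE, and lists no baseline covariate.
- **Visits.** Table 1 schedules PSQI at weeks 0, 4, 8, 12 and 20.
- **Primary outcome.** Section 2.6 bases the sample size on "change in PSQI score from baseline to Week 8".
- **Entry rule.** Section 2.5.1 requires participants to "Have a PSQI score > 7".
- **Missing data.** Section 2.12 fills dropout by last observation carried forward (LOCF), and section 2.6 allows for 20% attrition.

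**The concern.** A random intercept with independent residuals of constant variance gives compound symmetry: the same variance at each visit and the same correlation between any two visits. Several features of this trial make that doubtful. Baseline is truncated by the entry rule. The visit gaps are 4, 4, 4 and 8 weeks. The visits span the time before, during and after treatment. LOCF also copies values from one visit to the next.

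No baseline covariate is listed, so the natural reading is that baseline PSQI is one of the five responses. The SE of the baseline-to-week-8 contrast then comes from a within-person variance averaged over all visit pairs, not from the variability of that particular change. The primary CI and p-value depend on this SE.

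**Working it through.** **1. The plan's own figure.** Section 2.6 uses a difference of 3.8, a margin of 1.8, SD 4, one-sided alpha 0.025 and 90% power:

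n = 2 × 4² × (1.960 + 1.282)² / (3.8 − 1.8)² = 84.08, so 85 per group; 85 / 0.8 = 106.25, so 107.

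Both stated figures reproduce. If SD 4 is the SD of the change, the correct SE with 85 per arm is 4 × √(2/85) = 0.614. The covariance model does not enter this calculation.

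**2. Formula.** Take complete, balanced data (LOCF makes them so), categorical time and a group-by-time mean for every cell, with baseline as a visit:

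- pooled residual variance M = mean of the visit variances − mean of the between-visit covariances
- variance of the change that the model uses = 2M
- true variance of the change V = Var(week 0) + Var(week 8) − 2 Cov(week 0, week 8)
- SE ratio = √(2M / V)
- two-sided type I error = 2 × [1 − Φ(1.96 × ratio)]

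**3. Worked example (assumed values).** Baseline SD is 2.5, later SD 4, baseline-to-later correlation 0.3, later-to-later 0.7.

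- Mean variance = (6.25 + 4 × 16) / 5 = 14.05.
- The covariances are 0.3 × 2.5 × 4 = 3 (four pairs) and 0.7 × 16 = 11.2 (six pairs). Their mean is (12 + 67.2) / 10 = 7.92.
- M = 6.13 and 2M = 12.26 (SD 3.50). V = 6.25 + 16 − 6 = 16.25 (SD 4.03).
- Ratio = 0.869; type I error 8.9%.

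**4. Range over assumed patterns.**

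| Assumed pattern | SE ratio | Type I error |
|---|---|---|
| Compound symmetry | 1.00 | 5.0% |
| Baseline-to-later / later-to-later correlation 0.4/0.6, 0.3/0.7 or 0.5/0.8; baseline SD 0.7 to 1.0 of later SD | 0.96 to 0.80 | 6.1% to 11.7% |
| All correlations 0.5; baseline SD 0.9 to 0.7 of later SD | 1.03 to 1.08 | 4.4% to 3.5% |
| Compound symmetry with baseline truncated; correlation 0.3 to 0.8, 30 to 90% of baseline variance left | 1.003 to 1.093 | 4.9% to 3.2% |
| Correlation decaying with time, 4-week value 0.9 to 0.6 | 1.07 to 1.006 | 3.6% to 4.9% |
| Same, 4-week value 0.5 | 0.994 | 5.1% |

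**5. Effect of LOCF.** Data were simulated under exact compound symmetry, with 107 per arm and 20% random dropout filled by LOCF. Type I error was about 5.5 to 6.2%, depending on the correlation, dropout timing and mean change assumed. Carried values raise the later-to-later correlation, so the planned data handling breaks the assumption even if the complete data satisfy it.

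**6. If only post-baseline changes are modelled.** The model variance of the week-8 contrast then uses the average variance of change over the four visits, so error arises only where those variances differ. In rows 1 to 4 of the table the four variances are equal and the ratio is 1. Decaying correlation is the exception. With equal SDs scaled to 1 and a 4-week correlation of 0.9, the change variances are 0.2, 0.38, 0.542 and 0.819, with mean 0.485. The ratio is √(0.485 / 0.38) = 1.13, which is too large.

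**The case against.** **The article does not say that the random intercept is the only covariance element.** A statistical analysis plan that is not shown could add a residual structure or robust SEs. That is fair, and confirming that it does so would settle the point. But the article states its primary model outright, and as written that model carries the compound-symmetry restriction.

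**A reader might infer that the SE is wrong unless compound symmetry holds.** The documents do not support this. Compound symmetry is sufficient but not necessary: the SE is right whenever V = 2M, and decay with a 4-week correlation of 0.5 or 0.6 gives an error below 1%.

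**A reader might infer that the SE is simply understated.** That does not follow either. The two features most visible in the article, the entry threshold and the unequal spacing, mostly make the SE too large when taken alone. Understatement needs post-treatment visits that correlate more closely with each other than with baseline. That is plausible, but the article gives no correlations. LOCF also pushes toward understatement, more modestly.

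**A reader might add a multiplicity problem over the four post-baseline visits.** That is a separate, conditional issue. Section 2.6 names week 8, and nothing says that success may be claimed at any visit.

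**The size depends on how the response is set up.** This stands. Section 2.12 does not say whether the response is the raw score or the change, and modelling changes removes the understatement in the settings examined.

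**Conclusion.** The point holds as a recommendation on the choice of analysis. As written, the model can misstate the SE of the primary contrast in either direction, and the documents do not fix which. The range of 0.80 to 1.09 for the SE ratio, and about 12% to 3% for type I error, applies with baseline as a visit and rests on assumed SDs and correlations. In the settings where the SE is too small, the error is smaller if only post-baseline changes are modelled.

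The damage is confined to the SE, CI and p-value. With LOCF-completed data and categorical time the point estimate does not depend on the covariance choice, and the planned 85 and 107 per group stand. It should be changed because the primary inference can be protected at almost no cost, not because the result is known to be biased one way.

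**What to change.** In section 2.12, or in the analysis plan if it is not already there:

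- Treat visit as categorical.
- Replace the random intercept by an unstructured within-participant covariance, fitted by REML with Kenward-Roger degrees of freedom.
- Name robust SEs as the fallback if the model does not converge.
- Name the week-8 group contrast in change from baseline as the single primary estimate.

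This is a change of wording and one REPEATED statement in SAS. With five visits, an unstructured covariance has 5 × 6 / 2 = 15 parameters, against 2 for the random-intercept model. With 214 participants that cost is negligible.

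### The trial is sized to show that EA beats SEA by more than 1.8 PSQI points at week 8, but the analysis section only tests for a difference, without the margin

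*Protocol article*

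**What the plan says.** Protocol article, Sample size calculation (2.6): the primary outcome used for sizing is "change in PSQI score from baseline to Week 8". The aim is stated as follows: "A superiority trial design employing a two-sample mean comparison was used to assess whether EA demonstrates clinically meaningful superiority over SEA". The margin is 1.8 PSQI points, taken from published minimal clinically important differences of 1.69 to 1.80. It is subtracted from the expected difference of 3.8 in the denominator of the formula. The test is set at "a one-sided significance level α = 0.025" with 90% power, giving 85 per group, 107 after 20% attrition and 214 in total.

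Protocol article, Statistical analysis (2.12): primary and secondary outcomes are analysed with one linear mixed model with group, time and their interaction, and a random intercept per participant. Estimates are to be given with 95% confidence intervals. The only decision criterion is this: "All statistical tests will be two-sided", with significance at p < 0.05. The section names no margin, no shifted null, no comparison of the interval with 1.8 and no week-8 contrast. Table 1 schedules PSQI at weeks 0, 4, 8, 12 and 20.

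**The concern.** The two sections fix different hypotheses for the primary outcome. In 2.6 the null is a benefit of at most 1.8 points. In 2.12 a two-sided model p-value with no margin stated has, by ordinary reading, a null of zero.

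The 90% power and 2.5% error rate in 2.6 therefore belong to a test that 2.12 does not describe. A significant result under 2.12 could be taken to deliver the clinically meaningful superiority the trial was built to show, even when the true benefit does not exceed the protocol's own threshold for a meaningful difference. With two readings open, the choice between them could also be made after the result is known.

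**Working it through.** **Inputs, all from 2.6.**
- Expected difference ε = 3.8, from "PSQI scores decreased by 5.67 in the EA group and 1.83 in the SEA group" (5.67 − 1.83 = 3.84, rounded).
- Margin δ = 1.8.
- SD: "assumed a standard deviation σ = 4".
- z = 1.960 (one-sided 0.025) and 1.282 (90% power).
- Allocation 1:1, attrition 20%.

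Below, the difference is the PSQI reduction under EA minus that under SEA, so positive values favour EA.

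**Reproducing the stated size.**
- n = (1.960 + 1.282)² × 4² × 2 / (3.8 − 1.8)² = 84.08, rounded up to 85 per group.
- 85 / 0.8 = 106.25, rounded up to 107 per group, 214 in total.

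Both figures agree with the protocol.

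**The same inputs without the margin.**
- n = (1.960 + 1.282)² × 4² × 2 / 3.8² = 23.3, rounded up to 24 per group.
- 24 / 0.8 = 30 per group, 60 in total.

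The margin is thus what produces 214.

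**Observed difference each rule requires.** The standard error is SE = 4 × √(2/n). The test against zero needs 1.96 × SE; the margin test needs 1.8 + 1.96 × SE.

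| n per arm | SE | Needed against zero | Needed against 1.8 |
|---|---|---|---|
| 85 | 0.614 | 1.20 | 3.00 |
| 107 | 0.547 | 1.07 | 2.87 |

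The row for 107 applies if all randomised participants enter the analysis, as intention-to-treat with last observation carried forward would imply.

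**Probability that each rule is met.** For a true difference d, the test against zero is met with probability Φ(d/SE − 1.96), and the margin test with Φ((d − 1.8)/SE − 1.96).

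| True d | Against zero, n = 85 | Against 1.8, n = 85 | Against zero, n = 107 | Against 1.8, n = 107 |
|---|---|---|---|---|
| 1.2 | 50% | 0.2% | 59% | 0.1% |
| 1.8 | 83% | 2.5% | 91% | 2.5% |
| 2.5 | 98% | 21% | >99% | 25% |
| 3.8 | >99.9% | 90.3% | >99.9% | 95.5% |

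For example, at d = 1.8 and n = 85: Φ(1.8/0.6136 − 1.96) = Φ(0.97) = 0.83 against zero, and Φ(−1.96) = 0.025 against the margin.

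**Difference detectable against zero.** With 85 per arm and 90% power this is 3.242 × 0.6136 = 1.99 points.

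**The case against.** The strongest reply is that the sections are compatible. 2.6 supplies the hypothesis, endpoint and margin. 2.12 supplies the model and a 95% confidence interval, whose lower limit is exactly the one-sided 0.025 bound used in 2.6. Comparing that limit with 1.8 is the margin test, so only a linking sentence is missing, and that might sit in an analysis plan not shown. In addition, 2.12 nowhere writes that the null is zero or that p < 0.05 will be reported as clinically meaningful superiority.

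Several parts of this stand:
- Sidedness is not a fault: one-sided 0.025 and two-sided 0.05 share the critical value 1.96.
- The zero null is the default reading, not protocol text.
- Week 8 is named in 2.6, and a group-by-time model can estimate the difference there, so its absence from 2.12 is only a supporting point.
- Rejecting zero when the true difference is 1.8 is a correct rejection of zero. It becomes an error only if it is read as exceeding the margin.
- Better than sham and not shown to be better by more than 1.8 can both be true of the same data.

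The conclusion does not change. 2.12 does state a criterion, it is p < 0.05, and it does not test the hypothesis for which 2.6 sized the trial. That is a mismatch between two stated sections, not a detail left out of a condensed article. A separate plan that added the margin would still leave these two sections to be reconciled.

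**Conclusion.** The concern holds: the analysis as written does not test the powered hypothesis. For 85 evaluable per arm, any observed benefit between about 1.20 and 3.00 points (1.07 and 2.87 for 107) meets the criterion in 2.12 but not the one implied by 2.6. At a true benefit equal to the margin, the criterion in 2.12 is met 83% to 91% of the time, against the 2.5% that 2.6 allows for claiming more than 1.8.

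These figures rest on the protocol's SD of 4, a normal approximation and a simple two-sample comparison at week 8; the mixed-model standard error may differ somewhat. The mismatch itself depends on none of them. It must be settled before unblinding, because it decides whether the primary outcome counts as a success.

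**What to change.** Preferred: in 2.12 name one confirmatory test, the model-based difference between EA and SEA in PSQI change at week 8. Declare superiority by the margin only if the lower limit of its two-sided 95% confidence interval, expressed as benefit of EA, exceeds 1.8. Report the p-value against zero as supportive, and weeks 4, 12 and 20 as secondary. The sample size of 85/107/214 and the 90% power then stand as stated.

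Alternative, if a test against zero is what the sponsor intends: rewrite 2.6 without the margin and remove the claim of clinically meaningful superiority. Then justify the sample size on the new basis: 85 per arm gives over 99.9% power at 3.8 and 90% power at 1.99.

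The preferred fix costs one or two sentences before unblinding and no extra participants. Its price is a stricter success criterion, which is the one 2.6 was calculated for. The alternative needs the sample size section rewritten and leaves the trial with a weaker claim.
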